### Randomization and Concealment

The residents with dementia recruited by nursing assistants will be allocated to either the CG or IG. This allocation will be performed by cluster randomization as it is not possible to blind participants, nursing assistants, or study personnel regarding group allocation. Participants in the CG will only receive conventional treatment such as individualized medication, standard care, or therapeutic applications for 18 weeks. Participants in the IG will receive the individualized exercise program in addition to conventional treatment. To ensure equal conventional treatment for the IG and CG during the intervention, it will be continuously documented.

### Data Management

#### Patient Documentation

The flow of participants will be organized and documented with an Excel documentation file. The participating nursing assistants will be assigned a 2-digit ID (pseudonymization of the data). All personally identifiable information will be documented in a separate Excel file and will be stored separately. The residents with dementia trained by nursing assistants will receive a 3-digit ID, where the first digit will encode the assignment to IG or CG. The collection and storage of the data will be performed separately. Only selected members of the project team will have access to uncoded data. The InCoPE-App is not connected to the internet to ensure security of personal data during the study. After the end of the 18-week intervention, collected data will be transferred manually via cable and manually stored on a computer that is not connected to the internet.

The collection and retrieval of the data from the questionnaires focusing on usability will be done manually (paper and pencil) and via SoSciSurvey. The entered data will be checked for completeness, validity, and plausibility by a member of the research team.

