### Statistical Methods

All analyses will be performed using SPSS 27.0 (IBM Corp, Armonk, NY). Prior to analysis, plausibility (eg, considering range and distribution) will be checked to minimize errors. The quantitative analysis comprises the evaluation of the usability questionnaires, which will be analyzed with respect to the corresponding guidelines and will be compared with representative data.

The baseline values of physical and cognitive performance will be compared between IG and CG using chi-square tests for categorical data, Mann-Whitney *U* tests for nonparametric variables, and t tests for continuous and normally distributed parameters. Normal distribution will be checked with the Shapiro-Wilk test. Means and standard deviations will be calculated for normally distributed data, and medians and interpercentile ranges will be calculated for non-normally distributed data. A 2-factor ANOVA with repeated measurement will be used to identify treatment effects. In addition, 95% confidence intervals and partial Eta² will be calculated. The log events will be summarized and analyzed descriptively. Potential effects among subgroups based on varying physical or cognitive performance, gender, fear of falling, and logged events (completed training sessions, average duration of the training sessions) will be investigated using chi-square tests and *t* tests.

Qualitative content analysis of the field notes will be conducted [48]. The interviews will be fully transcribed and checked for accuracy. The entire coding process will be independently performed by 2 scientists. The transcripts will be reviewed to identify meaningful content-related aspects. These aspects will be systematically described using a category system. Research questions and interview guidelines will be consulted to deductively derive the main categories. Subcategories will be inductively developed based on the findings (eg, by subsumption). The category system will be tested by 2 scientists who will independently test-code several parts of the qualitative material and subsequently adapt the categories and their definitions. The 2 coding systems will eventually be merged by consensual coding where consensus will be reached.

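### The resident ID carries the trial arm in its first digit, which needlessly works against masked checking and cleaning of the resident data

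*Protocol article*

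**What the plan says.** Four places in the protocol article bear on this.

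- **Data Management, Patient Documentation (residents).** Each resident gets a three-digit identifier, "where the first digit will encode the assignment to IG or CG".
- **Data Management, Patient Documentation (other handling).** Nursing assistants get a two-digit code, with no arm element stated. Identifying information goes into a separate file, and "Only selected members of the project team will have access to uncoded data". That restriction concerns identity, not the arm. The section closes with "The entered data will be checked for completeness, validity, and plausibility by a member of the research team", directly after a sentence on how the usability questionnaires are collected.
- **Statistical Methods.** "Prior to analysis, plausibility (eg, considering range and distribution) will be checked to minimize errors". The text does not say who does this, whether the arm is hidden, or what range or distance makes a value implausible.
- **Randomization and Concealment.** Cluster randomization is chosen because "it is not possible to blind participants, nursing assistants, or study personnel regarding group allocation".

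The article does not describe replacing the resident ID with a neutral code before checking or analysis.

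**The concern.** Delivery of an exercise programme cannot be masked, and here the nursing assistants who run the tests know the arm. Handling of the recorded values is a separate step. Someone deciding whether a Timed Up & Go time is a recording error does not need to know the arm, and is better placed without that knowledge.

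The numbering rule takes that option away for any file that carries the resident ID. The plausibility check leaves room for judgement because it names range and distribution as considerations but sets no limits. The team making the judgement built the app and says in the Abstract and the Discussion that it expects improvement. If a few extreme values are queried, knowledge of the arm could influence which are kept, corrected or set aside. With 22 residents per arm, single values carry weight, and several resident outcomes are listed as primary in Table 1, so the occasion recurs.

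**Working it through.** The point turns on the text and not on a figure in the plan, so there is no stated number to reproduce.

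**Step 1: does the ID disclose the arm?** Yes. The rule for the first digit is explicit, and no step undoes it.

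**Step 2: whose data are affected?** Only data filed under the resident ID: quality of life, MMSE, digit span, the physical tests and the resident-level secondary measures. The usability questionnaires are completed by nursing assistants, whose code has no stated arm digit. The article does not say which identifier the analysis file carries, so the conclusion is conditional on that file using the resident ID.

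**Step 3: which decisions are exposed?**

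- *Plausibility check in Statistical Methods:* exposed. It precedes all analyses and has no stated limits.
- *Checking sentence in Patient Documentation:* weak support. From its position it most naturally refers to the usability questionnaires.
- *Normality:* not a free judgement. Statistical Methods assigns it to the Shapiro-Wilk test.
- *Exclusion of extreme values:* no rule is described, so what follows a failed plausibility check is open.

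**Step 4: how much could one decision matter?** This is an illustration.

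- Input from Sample Size: n = 22 per arm.
- Assumption: each dropped value lies d = 2.5 SD from the mean of the values that remain, and all dropped values lie on the same side.
- If k of n values are dropped, the full mean equals the mean of the remaining values plus k × d / n. The shift on dropping them is therefore k × d / n.
- One value: 1 × 2.5 / 22 = 0.114 SD.
- Two values: 2 × 2.5 / 22 = 5 / 22 = 0.227 SD.

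For comparison, the standard error of a difference between two arms of 22, ignoring clustering, is √(2/22) = 0.302 SD. One such exclusion is 0.114 / 0.302 = 0.38 of a standard error, and two are 0.227 / 0.302 = 0.75. Clustering would enlarge the standard error and reduce these ratios. The documents give no basis for expecting any particular number of such values.

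**The case against.** The strongest reply is that the design is openly unmasked. Randomization and Concealment says so for study personnel, and no masked data manager or analyst is promised. A reader might infer that the arm digit breaks the trial's blinding; it does not, because there is no stated blind to break and the numbering is consistent with the rest of the article. That much stands. It does not answer the narrower point. The statement that study personnel cannot be masked is true of those who train and support the homes, but it need not be true of a person checking rows of test times.

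A second reply is that masked data review usually belongs in a data management plan or SAP, which is not shown. That would dispose of a complaint about a missing step. Here, however, the article itself fixes an identifier that works against such a step.

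Third, the gain is limited, and this stands. All residents of a home share an arm, so home or assistant labels can reveal it. So can app records that exist only for the intervention group. Research staff also meet the assistants and stay in contact with them.

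Fourth, the larger exposure lies elsewhere. The assistants instruct and time the tests, and quality of life uses a caregiver-administered version. A reader might take the ID to be the source of unblinded outcome assessment. It is not, and changing it would leave that untouched.

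A reader might also see harm in the ID having to wait for the allocation. Study Design has homes randomized before residents are recruited, so the arm is known by then under any numbering.

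**Conclusion.** The point holds in a limited form. The arm-coded resident ID lets anyone handling resident data under it see the allocation while making plausibility judgements without stated limits, and the article gives no reason for coding the arm there. This is an avoidable obstacle to masked data handling, which remains achievable at least in part.

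A reader might go further and infer that everyone sees the arm on every record, or that arm-aware deletion of outliers is planned. The documents support neither: only resident IDs carry the digit, and no deletion rule is described.

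The shifts of 0.11 and 0.23 SD show what one or two one-sided exclusions could do in an arm of 22. They rest on an assumed distance of 2.5 SD and an assumed count, and they do not estimate bias in this trial. The conclusion also assumes that the cleaning or analysis file uses the resident ID and that no unpublished document re-codes it. Severity: a minor, cheap improvement.

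**What to change.** Use a resident ID with no arm digit. According to Results, enrolment began in October 2021, so where IDs have already been issued, replace them with neutral codes when the data are exported from the tablets. Then:

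1. Hold the link between code and arm in a separately stored file, as Patient Documentation already does for identifying information.
2. Remove home and assistant labels from the cleaning file, and keep app logs that exist only for the intervention group out of it.
3. Complete the plausibility and outlier decisions on the resident outcomes, record each one with its reason, and lock the data.
4. Merge the arm, the cluster labels and the app logs only after the lock.

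In Randomization and Concealment, limit the statement on study personnel to those involved in delivery and assessment, and say that the resident data are checked without the arm.

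The cost is one re-coding step and one merge, plus the care needed to restore cluster labels correctly. Masking will be partial, and the outcome tests themselves stay with unmasked assistants.

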#### Data Monitoring

This study represents a non-drug intervention focusing on health benefits among people with dementia while undergoing an individualized exercise program delivered by trained nursing assistants who use the InCoPE-App. We do not expect any harmful effects nor adverse events related to the individualized exercise program. All exercises that are part of the program have been used in people with dementia before, and all questionnaires used to examine usability are derived from validated instruments that have been widely used in prior research. The study is thus considered to have minimal to no risks for participants, and establishing a data monitoring committee is not required. An interim analysis is not planned.

### Statistical Methods

All analyses will be performed using SPSS 27.0 (IBM Corp, Armonk, NY). Prior to analysis, plausibility (eg, considering range and distribution) will be checked to minimize errors. The quantitative analysis comprises the evaluation of the usability questionnaires, which will be analyzed with respect to the corresponding guidelines and will be compared with representative data.

The baseline values of physical and cognitive performance will be compared between IG and CG using chi-square tests for categorical data, Mann-Whitney *U* tests for nonparametric variables, and t tests for continuous and normally distributed parameters. Normal distribution will be checked with the Shapiro-Wilk test. Means and standard deviations will be calculated for normally distributed data, and medians and interpercentile ranges will be calculated for non-normally distributed data. A 2-factor ANOVA with repeated measurement will be used to identify treatment effects. In addition, 95% confidence intervals and partial Eta² will be calculated. The log events will be summarized and analyzed descriptively. Potential effects among subgroups based on varying physical or cognitive performance, gender, fear of falling, and logged events (completed training sessions, average duration of the training sessions) will be investigated using chi-square tests and *t* tests.

Qualitative content analysis of the field notes will be conducted [48]. The interviews will be fully transcribed and checked for accuracy. The entire coding process will be independently performed by 2 scientists. The transcripts will be reviewed to identify meaningful content-related aspects. These aspects will be systematically described using a category system. Research questions and interview guidelines will be consulted to deductively derive the main categories. Subcategories will be inductively developed based on the findings (eg, by subsumption). The category system will be tested by 2 scientists who will independently test-code several parts of the qualitative material and subsequently adapt the categories and their definitions. The 2 coding systems will eventually be merged by consensual coding where consensus will be reached.

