Examination of the effects of the InCoPE-App on physical and cognitive performance in people with dementia will be determined based on the listed variables in Table 1. The primary outcomes will be assessed before and after the 18-week intervention. To assess quality of life, the 13-item caregiver-administered version of Quality of Life-Alzheimer’s Disease (QOL-AD) [27] will be applied. The QOL-AD is a valid and reliable tool (internal reliability, α=0.88-0.89; test-retest reliability for caregivers, 0.92) [27]. Global cognition will be assessed with the MMSE [28]. The questionnaire will be implemented in the InCoPE-App. The MMSE easily assesses 7 areas of cognitive function, with sufficient test-retest reliability (0.80-0.95) [28,36]. To assess executive function, the Digit Span Test [29] will be administered. The Digit Span Test consists of 2 parts: forward and backward. Participants will be asked to repeat a sequence of 3 to 9 digits forward and of 2 to 8 digits backward. The InCoPE-App will be used to document the given answers. The Digit Span is a reliable and valid test [37].

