The chosen tests for physical performance are considered reliable tests in a geriatric setting. Among people with dementia, the intraclass correlation coefficients for test-retest reliability are 0.79-0.82 for FICSIT-4, 0.83-0.89 for 6MWT, 0.78-0.88 for the modified 30s CST, and 0.72-0.99 for the TUG test [38,39]. The 95% minimal detectable changes are 58.9%-71.1% for FICSIT-4, 31.6%-41.5% for 6MWT, 33.2%-45.7% for the modified 30s CST, and 15.8%-39.6% for the TUG test [38,39]. No information about content and construct validity is available in this setting.

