### Sample Size

The sample size for the number of nursing assistants who will evaluate the InCoPE-App with regard to usability was defined using a probabilistic model of problem discovery for formative user research [34]. We defined a sample size comprising 22 participants to have a 90% chance of observing with a probability of 0.1. In the second study phase, outcomes also include usability in addition to the effectiveness of the InCoPE-App with respect to adaptations in physical and cognitive performance in people with dementia. For this reason, each participant will recruit 2 appropriate residents with dementia in accordance with our inclusion and exclusion criteria. We anticipate that our calculated sample size (N=44: intervention group [IG], n=22; control group [CG], n=22) will be appropriate to examine potential trends toward effectiveness of the InCoPE-App.

This sample size allows detection of moderate effects calculated using an ANOVA with repeated measures for within and between interactions. The calculation of the sample size with G*Power version 3.1.9.2 (Heinrich Heine University of Dusseldorf, Germany [47]; effect size ηp² = 0.07, α error probability .05, power 0.95) resulted in 44 participants.

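### The planned group-by-time ANOVA is a change-score test; adjusting for the baseline value already collected would usually be more precise, at almost no cost

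*Protocol article*

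**What the plan says.** Three parts of the protocol article bear on this.

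- **Timing.** Under Primary Outcomes: "The primary outcomes will be assessed before and after the 18-week intervention". Table 1 agrees, with one pre and one post value for quality of life, cognition and the physical tests. The three-weekly tests in the app are described as a means of adjusting the program.
- **Analysis.** Under Statistical Methods: "A 2-factor ANOVA with repeated measurement will be used to identify treatment effects". Confidence intervals and partial eta squared are added. No baseline covariate is named. The same section plans significance tests of the two arms at baseline: "The baseline values of physical and cognitive performance will be compared between IG and CG using chi-square tests for categorical data", with Mann-Whitney and t tests for the other variables. It attaches no consequence to their results.
- **Sample size.** The number of residents ("N=44: intervention group [IG], n=22; control group [CG], n=22") was "calculated using an ANOVA with repeated measures for within and between interactions", with "effect size ηp² = 0.07, α error probability .05, power 0.95". The pre-post correlation that such a calculation needs is not given.

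**The concern.** A group-by-time interaction with two time points subtracts the whole baseline value from the post value, so the baseline weight is fixed at 1 whatever the data show. When the pre-post correlation is below 1, that weight is too large. Two things follow. The treatment estimate usually has a larger variance than it need have. It also depends on how the arms happened to differ at the start, because the arm that begins worse tends to look as if it gained more.

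Testing the baseline difference for significance does not help. At 22 per arm such tests have little power to show an imbalance that matters, and a result in either direction leaves the estimate unchanged. At stake are the precision and stability of every effectiveness estimate in a trial that itself lists its small sample as a limitation. The validity of the analysis under proper randomisation is not at stake.

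**Working it through.** **Inputs.** 22 residents per arm, N = 44, partial eta squared 0.07, alpha 0.05 and power 0.95 (Sample Size); two time points (Primary Outcomes); pre-post correlation rho not stated. The nearest figures are test-retest reliabilities in the Primary Outcomes section: "0.79-0.82 for FICSIT-4, 0.83-0.89 for 6MWT, 0.78-0.88 for the modified 30s CST, and 0.72-0.99 for the TUG test" for the physical tests, 0.80 to 0.95 for the MMSE and 0.92 for the caregiver QOL-AD.

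**Step 1: the plan's own N.** For the within-between interaction with two groups and m = 2 measurements, f² = 0.07/0.93 = 0.0753, noncentrality = f² × N × m/(1 − rho), with 1 and N − 2 degrees of freedom. At rho = 0.5 and N = 44 the noncentrality is 0.0753 × 44 × 2/0.5 = 13.2 and power is 0.945. Power of 0.95 needs N = 46, or exactly 44 if f is rounded up to 0.28. Other correlations do not fit: N = 54 at 0.4, 38 at 0.6 and 20 at 0.8. So rho = 0.5 is the value that approximately reproduces the plan's figure.

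**Step 2: the interaction is a change-score test.** On a simulated data set of 44 residents, the interaction F and the squared t on change scores were both 0.04429. The identity is exact.

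**Step 3: variance with and without adjustment.** With equal pre and post variances (SD = 1), independent residents and n per arm:

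- change score: (2/n) × 2(1 − rho)
- baseline-adjusted: (2/n) × (1 − rho²)
- ratio: (1 − rho²)/[2(1 − rho)] = (1 + rho)/2

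Estimating the slope multiplies the adjusted variance by 1 + 1/(N − 4) = 1 + 1/40 = 1.025.

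| rho | ratio | reduction | reduction at N = 44, slope estimated |
|---|---|---|---|
| 0.5 | 0.75 | 25% | 23% |
| 0.6 | 0.80 | 20% | 18% |
| 0.7 | 0.85 | 15% | 13% |
| 0.72 | 0.86 | 14% | 12% |
| 0.8 | 0.90 | 10% | 8% |
| 0.89 | 0.945 | 5.5% | 3% |
| 0.92 | 0.96 | 4% | 1.6% |
| 0.99 | 0.995 | 0.5% | −2% (a small loss) |

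In 20,000 simulated trials of 22 per arm, the variance ratio was 0.77 at rho 0.5 and 0.93 at rho 0.8. The formula with the slope factor gives 0.75 × 1.025 = 0.77 and 0.90 × 1.025 = 0.92.

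**Step 4: dependence on imbalance.** The chance baseline difference has standard error √(2/22) = 0.30 SD. In the simulations the change-score estimate moved by −0.49 (rho 0.5) or −0.19 (rho 0.8) per unit of baseline difference. The adjusted estimate moved by about 0. A one-standard-error imbalance therefore shifts the change-score estimate by about 0.30 × 0.49 = 0.15 SD, or 0.30 × 0.19 = 0.06 SD. Both estimators averaged to the same value, but in a single trial they differed with an SD of 0.16 (rho 0.5) or 0.07 (rho 0.8) outcome SD.

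**Step 5: power.** Taking the design at rho = 0.5 and the 25% reduction, with one degree of freedom lost but without the slope factor, power at N = 44 rises from 0.945 to 0.984. The N for 0.95 power falls from 46 to 36. These figures also ignore clustering.

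**The case against.** The strongest reply is that nothing here is wrong. The planned ANOVA is unbiased under proper randomisation, it tests the very interaction on which the sample size was based, and the effectiveness aim is only to look for trends. The article is condensed, and a statistical analysis plan might add covariates. The baseline tests trigger no decision and so do no harm.

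Most of that is fair, and it limits the point to an improvement. It does not remove it. The article states its model instead of leaving it open, and agreement with the sample-size basis is no obstacle to an analysis that at the implied correlation has more power.

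Three further objections stand and limit the claim.

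- **The size of the gain is conditional.** The article gives no 18-week correlation. Reliabilities are plausibly upper limits over such an interval in a progressive disease, but that is an assumption. Most of those cited would put the gain below 10%.
- **The formula ignores clustering.** It treats residents as independent, whereas homes are randomised. The gain then also depends on correlation at home level, so it cannot be read as a number of extra residents.
- **Imbalance may not be chance.** Under Study Design, homes are randomised and nursing assistants recruit afterwards. Under Randomization and Concealment, nobody is blinded. If residents are selected differently by arm, the two analyses can disagree systematically, and adjusting for an imperfectly measured baseline need not remove the bias.

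**Conclusion.** The point holds as a free improvement in precision and robustness. The planned interaction is a change-score test. Under independent residents and equal variances, baseline adjustment cuts the variance by 25% at rho 0.5 (about 23% at N = 44) and by 10% at rho 0.8 (about 8%). If the 18-week correlation approached the higher cited reliabilities, the gain would shrink to 4% at 0.92 and 0.5% at 0.99, where the cost of estimating the slope would cancel it.

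A reader might infer more than this, and the documents do not support it:

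- *That the planned ANOVA is invalid.* It is not, given proper randomisation.
- *That a gain of 10 to 25% is assured.* That range presupposes a correlation between 0.8 and 0.5, which is not stated.
- *That the two analyses give the same answer.* They target the same expected effect under randomisation, but the estimates can differ within one trial.
- *That adjustment cures imbalance of any origin.* It deals with chance imbalance. It offers no guarantee against selection after randomisation.
- *That the number of homes is small or that power is short.* The text gives no number of homes, and the stated power is approximately reproduced at rho 0.5. Any loss of power from clustering is a separate question, not settled here.

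**What to change.** For each effectiveness outcome, model the post value on group with the resident's own baseline value as covariate and home as a random effect, to respect the cluster randomisation. Report the adjusted mean difference with its 95% CI, in the units of the outcome, as the treatment effect. Replace the baseline significance tests with a descriptive table by arm. Record this model before outcome data are analysed.

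The cost is a revised paragraph in Statistical Methods and different SPSS syntax. No further data, visits or residents are needed. The sample-size text should add a sentence saying that N = 44 was calculated for the unadjusted interaction and which pre-post correlation was assumed.

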## Methods

### Study Design

This study combines the evaluation of the usability of the InCoPE-App with the effectiveness of the individualized exercise program concerning cognitive function, physical performance, and quality of life. Thus, a mixed methods design with different methodological components will be used. The evaluation of the usability and effectiveness of the InCoPE-App will be based on the use of the app for a duration of 18 weeks in a nursing home setting. This approach represents a field study and will be carried out as a cluster-randomized controlled trial in which the InCope-App will be used with people with dementia and the individualized, multidomain exercise program will be delivered by nursing assistants with the help of the app. The nursing homes will be cluster randomized, and each nursing assistant will subsequently recruit at least 2 people with dementia (see Figure 1).

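### Nursing homes are randomised, but the power calculation and the repeated-measures ANOVA treat the 44 residents as independent, so intervals are too narrow and the stated 5% error and 0.95 power do not hold if changes are correlated within homes

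*Protocol article*

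**What the plan says.** **Design.** Under Study Design the trial "will be carried out as a cluster-randomized controlled trial", and "The nursing homes will be cluster randomized, and each nursing assistant will subsequently recruit at least 2 people with dementia". Randomization and Concealment repeats this: "This allocation will be performed by cluster randomization as it is not possible to blind participants, nursing assistants, or study personnel regarding group allocation". There is a second level of nesting. Under Sample Size, "each participant will recruit 2 appropriate residents with dementia in accordance with our inclusion and exclusion criteria", where the participant is a nursing assistant.

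**Sample size.** The same section obtains 44 residents (22 per group) from G*Power, using a repeated-measures ANOVA for the within-between interaction with "effect size ηp² = 0.07, α error probability .05, power 0.95". It gives no number of homes, intraclass correlation or design effect. Strength and Limitations repeats that the sample suffices for moderate interactions and names only its small size as a limitation.

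**Analysis.** Under Statistical Methods, "A 2-factor ANOVA with repeated measurement will be used to identify treatment effects", with 95% confidence intervals and partial eta squared. No random effect, robust variance, generalised estimating equation or cluster-level analysis appears anywhere in the article.

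**The concern.** With two groups and two occasions, the two factors are group and time. The repeated factor accounts for the two measurements within a resident. It does not account for residents within a home or within a nursing assistant.

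Residents of one home share staff, usual care and pandemic restrictions. In the intervention group they also share the person who delivers the programme and runs the tests. Their changes over 18 weeks may therefore be correlated. The planned test takes 42 error degrees of freedom from 44 residents, while the information on the group effect is limited by the number of homes.

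All seven resident-level primary measures in Table 1 are affected: QOL-AD, MMSE, digit span, TUG, 6-meter walk, chair stand and FICSIT-4. On each of them a false positive is more likely than stated, and the real power is lower than stated.

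**Working it through.** **1. Reproduce the plan's figure.**
- Inputs from Sample Size: partial eta squared 0.07, alpha 0.05, power 0.95, N = 44. From Outcomes: 2 measurements.
- Assumed, because not stated: correlation between measurements rho = 0.5, sphericity 1.
- f² = 0.07/0.93 = 0.0753, so f = 0.274.
- Noncentrality λ = f² × N × m/(1 − rho) = 0.0753 × 44 × 2/0.5 = 13.25, with 1 and 42 degrees of freedom.
- Power at N = 44 is 0.945. Power 0.95 needs N = 46, or exactly 44 if f is rounded to 0.28.
- Other values of rho do not reproduce 44: 0.3 gives 64 and 0.6 gives 38.

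The stated 44 is therefore the answer for individually randomised residents.

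**2. Which correlation matters.** With two occasions, the group-by-time F test is the two-sample t test on change scores. Stable differences between homes cancel in the change. The relevant ICC is thus that of the change score, not that of the baseline level.

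**3. Formulas.** With k homes of equal size:
- Design effect DE = 1 + (44/k − 1) × ICC. The true standard error is about √DE times the planned one.
- Power uses λ = 13.25/DE with 1 and k − 2 degrees of freedom.
- Type I error of the planned test comes from simulation of change scores under no effect, with 44 residents in k homes.

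**4. Results.** k and the ICC are assumptions. Each range runs from ICC 0.01 to ICC 0.10.

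| Homes (k) | DE | Type I error, nominal 5% | Power, k − 2 df |
|---|---|---|---|
| 22 | 1.01–1.10 | 5.0–6.2% | 0.93–0.91 |
| 11 | 1.03–1.30 | 5.3–8.7% | 0.89–0.81 |
| 6 | 1.06–1.63 | 5.7–12.7% | 0.75–0.58 |
| 4 | 1.10–2.00 | 5.9–17.3% | 0.47–0.31 |

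Repeated simulations agree within a few tenths of a percentage point (for 4 homes at ICC 0.01, for example, 5.9% and 6.3%). Coverage of the nominal 95% interval is the complement: about 87% for 6 homes and 83% for 4 homes at ICC 0.10.

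**5. Two sources of power loss.** For 4 homes the design effect alone, with 42 degrees of freedom kept, takes power to 0.92–0.71. The rest of the fall to 0.47–0.31 comes from having only 2 degrees of freedom. This is why power drops with few homes even at ICC 0.01.

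**6. Would a home random intercept repair it?** Write the score of a resident in home j as fixed part + u_j + resident effect + error, at both occasions. In post minus pre, u_j cancels, so the group-by-time test cannot see it. In simulated data with 6 homes and a change-score ICC of 0.10, the t values from such a model and from the planned test were the same (0.4737 and 0.4737; 0.8344 and 0.8344). Both rejected in 12.7% of 150 null runs, which is imprecise as a rate but identical for the two.

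**The case against.** **Left to the SAP.** A journal article leaves much to a fuller document. That does not help here. The article names the model and prints the power calculation, and neither fits the stated design. A SAP would have to replace this text, not complete it.

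**Exploratory aim.** Participants and Sample Size speak of trends toward effectiveness, and the number of residents follows from recruiting 22 nursing assistants for usability. This softens the consequence. It does not remove it, because the same section states alpha .05 and power 0.95, the analysis reports 95% intervals, and the effectiveness measures are listed as primary.

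**Size unknown.** This objection stands. A reader might infer that the planned test is badly anti-conservative, or that real power is near 0.6. The article does not support either as a fact. With about 22 homes of 2 residents and a small ICC, the inflation is negligible. The 6-home figures are one scenario among several, since no number of homes is stated. The k − 2 degrees of freedom are those of a home-level analysis; a mixed model may keep more when the estimated variance between homes is small. Unequal home sizes would push the other way.

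**Nursing assistant level.** With about 2 residents each, a separate variance for assistants is barely estimable. This is a fair limit on how far the model can go.

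**Conclusion.** The point holds and should be corrected before analysis. The unit of randomisation is the home, and both the power calculation and the named test ignore it. The direction is certain for any positive change-score ICC: intervals too narrow, type I error above 5%, power below the stated 0.95.

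The size is not certain. Over 4 to 22 homes and ICCs of 0.01 to 0.10, it runs from negligible (about 5% type I error, power 0.93) to serious (about 17%, power 0.31). These figures rest on rho = 0.5, equal or near-equal home sizes and no dropout, and the article states none of these.

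**What to change.** **Statistical Methods.** Replace the 2-factor ANOVA by a linear mixed model (SPSS MIXED) of the post score adjusted for baseline, or of the change score. Include a random effect for nursing home and use Satterthwaite-type degrees of freedom. If the repeated-measures form is kept, add a home-by-time random effect; a home intercept alone leaves the group-by-time test unchanged. Add nursing assistant within home only where it can be estimated. With very few homes, analyse home-level mean changes. Report the change-score ICC for each outcome.

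**Sample Size.** State the planned number of homes, the assumed change-score ICC, the design effect and rho, and restate the power. Change the claim of sufficiency in Strength and Limitations to match, and name clustering there.

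**Cost.** A paragraph of text and new syntax, wider intervals and a lower stated power. The analysis change needs no extra residents and can be made with enrolment under way. Keeping 0.95 power would need more homes or residents. With 5.5 residents per home and ICC 0.05 to 0.10, 44 × 1.225 = 54 to 44 × 1.45 = 64 residents, and these are lower bounds because they keep resident-level degrees of freedom.
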